### Trial participants

#### Overall description of the trial participants

This study will enroll subjects with cCSC with active leakage of fluid under the retina as evidenced on OCT scanning and further supported by findings on fluorescein angiography and ICG angiography, in at least one eye. If both eyes are eligible, then the eye with the longer duration of disease will be used as the study eye, except in cases where the disease is present for more than 18 months. In the latter case, which is an exclusion criterion, the other eye will be eligible for inclusion if the disease has been active for less than 18 months. If the nonstudy eye also has active disease, the choice to treat and the type of treatment in this eye may be chosen freely at the discretion of the responsible ophthalmologist.

Before enrolment, each subject must meet all of the following inclusion criteria and none of the exclusion criteria and agree to comply with the study requirements, including completion of all of the study visits.

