## Background

### Chronic central serous chorioretinopathy

Central serous chorioretinopathy (CSC) is a relatively common early-onset eye disease, characterized by an accumulation of leaked serous fluid under the retina, causing a detachment of the neuroretina. This subretinal fluid (SRF) leakage results from dysfunction of the retinal pigment epithelium (RPE), and the presence of choroidal congestion and thickening and hyperpermeability of the choroid implies an important role for choroidal abnormalities as an underlying cause for RPE dysfunction and SRF leakage in CSC [1–4].

Two main subtypes of CSC are generally distinguished: acute and chronic CSC (cCSC) [1–7]. Patients with acute CSC present with a sudden and marked central vision loss because of SRF leakage in the macula; this is due to a focal leak in the RPE that is visible on fluorescein angiography. Acute CSC generally has a favorable prognosis because the SRF often disappears spontaneously within 2 to 3 months, with either complete or almost complete recovery of vision. In contrast, cCSC is typically not self-limiting, and SRF persists for more than 3 months. Also, cCSC patients present at an older age, with a disease onset that is generally experienced as less sudden, and bilaterality in chronic CSC is common [8]. A history of acute CSC and/or an episode of acute vision loss compatible with acute CSC is present only rarely in chronic CSC patients [2, 8], which also points to a distinction between acute and chronic CSC. Patients with the cCSC phenotype have more diffuse multifocal leakage on fluorescein and indocyanine green (ICG) angiography, as well as irregularly distributed widespread RPE changes associated with varying degrees of more indistinct leakage on angiography (Fig. 1). Persistent serous neuroretinal detachments can cause progressive and irreversible photoreceptor damage, resulting in a poorer visual prognosis of cCSC as compared to acute CSC [2, 9, 10]. The etiology of CSC is largely unknown, but the use of corticosteroids is a risk factor, and possibly elevated cortisol levels, stress, “type A” personality, and pregnancy are also possible risk factors [1, 11–14]. The incidence of CSC is approximately six times higher in men than in women [1], although this male-to-female proportion seems to be less pronounced in cCSC and steroid-associated CSC. Recently, single-nucleotide polymorphisms in the *Complement Factor H* and *ARMS2* have been found to be associated with cCSC [15, 16].

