An overview of the assessments in the trial are as follows:OphthalmoscopyThis examination will be performed by one of the ophthalmologists to confirm the diagnosis. The pupils will have to be dilated with 1.0 % tropicamide and 2.5 % phenylephrine for ophthalmoscopy to be performed.Fundus photographyThe fundus photography will be taken with a Topcon TRC-50 series fundus camera. The photographs will be taken with a 50°-field centered on the area of the macula.Optical coherence tomography (OCT) imagingPatients will be examined by noninvasive OCT imaging. OCT shows the different layers of the retina and is the imaging modality of choice to visualize subretinal and intraretinal fluid, for instance in cCSC. This examination is performed during mydriasis (dilated pupils). OCT imaging will be carried out with a Spectralis HRA + OCT (Heidelberg Engineering, Heidelberg, Germany).Fundus autofluorescence imagingFundus autofluorescence is a noninvasive imaging technique that is able to register changes of autofluorescence intensity in the retina, for instance due to accumulation of lipofuscin in the RPE. Fundus autofluorescence imaging will be carried out with a Spectralis HRA + OCT (Heidelberg Engineering, Heidelberg, Germany).Fluorescein and indocyanine green (ICG) angiographyTo perform fluorescein and ICG angiography, intravenous injection of fluorescein and ICG is required. During the angiography procedure, both (fluorescein and ICG) dyes may be injected at the same time or separately. Fluorescein reveals the retinal vasculature and may show areas of fluid leakage through the RPE, whereas the ICG dye images the choroidal vasculature. The visualization of both the retinal vasculature and RPE permeability (by fluorescein angiography) and choroidal vasculature (by ICG angiography) is essential to image the areas of abnormal anatomy and leakage that may guide treatment. Images of the study eye are taken at set times: 0 to 1 minute (several images covering the arterial and venous filling phases), 3 minutes, 6 minutes, 10 minutes, 15 minutes, and 20 minutes. Images of the nonstudy eye will be taken at 1 minute, 6 minutes, and 20 minutes. All images will be acquired with Spectralis HRA + OCT (Heidelberg Engineering, Heidelberg, Germany).Best-corrected visual acuity (BCVA)BCVA will be assessed for both eyes at all evaluation visits. To measure BCVA, early treatment diabetic retinopathy study (ETDRS) visual acuity testing charts will be used at a distance of 4 meters.MicroperimetryAll patients will be examined by noninvasive microperimetry. This technique is able to measure retinal sensitivity to light, and follow-up pre- and post-treatment changes in retinal sensitivity at predetermined loci in the macula. By using a reliable eye tracking system, this microperimetry system is able to exactly locate the areas of retina that have been tested previously, in order to ensure testing of identically the same area at follow-up. Microperimetry according to a standard protocol takes 5 to 8 minutes for each eye and will be performed with non-dilated pupils.QuestionnairesEach participant will be asked to complete a quality-of-life questionnaire based on the National Eye Institute Visual Function Questionnaire (NEI-VFQ-25) [52], and the Cohen Stress Questionnaire [53] [http://www.centervue.com/product.php?id=639]. NEI-VFQ-25 is a reliable and validated 25-item version of the 51-item National Eye Institute Visual Function Questionnaire [54]. The questionnaire is especially useful in settings such as clinical trials, where interview length is an important consideration. The Cohen Stress Questionnaire is a validated questionnaire indicating the stress level patients have been exposed to during the month before disease onset.

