#### Secondary endpoints

For secondary endpoints, we will mainly look at three parameters that reflect the patient’s vision-related functioning. These three parameters are a standardized measurement of BCVA according to the ETDRS standards, a standardized measurement of sensitivity of the macula with microperimetry, and a standardized assessment of the patient’s vision-related quality of life using a validated questionnaire, the NEI-VFQ-25.

The secondary endpoints that will be assessed as a reflection of functional improvement after treatment include the following:Number of second treatments needed in each treatment arm.Mean change from baseline in ETDRS BCVA in the study eye at 6 to 8 weeks after treatment visit 1 and at 7 to 8 months after treatment visit 1, among the two treatment modalities.Mean change from evaluation visit 1 in ETDRS BCVA in the study eye at final evaluation (7 to 8 months after treatment visit 1), among those who required one treatment and those who required a second treatment, and among the two treatment modalities overall.Mean change from baseline in retinal sensitivity on microperimetry in the study eye at 6 to 8 weeks after treatment visit 1 and at 7 to 8 months after treatment visit 1 among the two treatment modalities.Mean change from baseline in the NEI-VFQ-25 questionnaire at 6 to 8 weeks after treatment visit 1 and at 7 to 8 months after treatment visit 1 among the two treatment modalities.An absence of SRF on evaluation with OCT scanning as compared to HSML treatment at 7 to 8 months follow-up after successful treatment (after treatment visit 1; “success” defined as an absence of SRF on OCT at 6 to 8 weeks after treatment).

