#### Exclusion criteria

The participant may not enter the study if any of the following apply:Any previous treatments for active CSC in the study eye.Current treatment with corticosteroids (topical or systemic), corticosteroid use within 3 months before the possible start of trial treatment, or anticipated start of corticosteroid treatment within the first 7 to 8 months from the start of the trial period.Evidence of other diagnosis that can explain serous SRF or visual loss.BCVA <20/200 (Snellen equivalent).Profound chorioretinal atrophy in central macular area on ophthalmoscopy and OCT.Myopia >6D.Visual loss and/or serous detachment on OCT <6 weeks.Continuous and/or progressive visual loss >18 months or serous detachment on OCT >18 months.No hyperfluorescence on ICG angiography.Intraretinal edema on OCT.Contraindications (relative) for PDT treatment (pregnancy, porphyria, severely disturbed liver function). Pregnancy will not be routinely tested in female patients, but the possibility of pregnancy will be discussed during eligibility screening.Contraindications (relative) for fluorescein angiography or ICG angiography (known allergies especially against shellfish, previous reactions).Soft drusen in treated eye or fellow eye, signs of choroidal neovascularization on ophthalmoscopy and/or fluorescein angiography/ICG angiography.

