#### Multivariate analysis

##### Analysis for the secondary endpoints

For the secondary endpoints, the following analyses will be performed:Anatomic results based on OCT scan (absence of SRF versus persistent SRF) at evaluation point 1 will be compared to the baseline.Number of subsequent treatments needed in each treatment arm.Mean change from baseline in ETDRS BCVA in the study eye at 6 to 8 weeks after treatment and at the end evaluation will be compared between the two treatment modalities.Mean change from evaluation point 1 in ETDRS BCVA in the study eye at final evaluation among those with subsequent and those without subsequent treatment will be compared between the two treatment modalitiesMean change from baseline in retinal sensitivity in the study eye to 6 to 8 weeks after treatment will be compared between the two treatment modalities.Mean change from baseline in the NEI-VFQ-25 questionnaire to 6 to 8 weeks after treatment will be compared among the two treatment modalities.

The first two analyses will be performed by the use of a cross-table. Furthermore, the continuous secondary variables will be analyzed using an ANCOVA model with baseline as and treatment as factor. For categorical secondary endpoints, a chi-square test will be performed. In addition, a logistic model with baseline as covariate and treatment as factor will be performed. The change from baseline in the NEI-VFQ-25 questionnaire results will be summarized descriptively.

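### The NEI-VFQ-25 is a whole-person score, but its planned analysis ignores the non-study eye, which may be treated freely: avoidable noise, and bias if that treatment differs by arm

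*Protocol article*

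**What the plan says.** Under Overall description of the trial participants, if the non-study eye is also active, "the choice to treat and the type of treatment in this eye may be chosen freely at the discretion of the responsible ophthalmologist". No time window is given, and the other arm's modality is not barred. The Background states that "bilaterality in chronic CSC is common". The prior-treatment exclusion covers one eye only: "Any previous treatments for active CSC in the study eye". The Summary of trial design calls the trial open label.

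The Secondary endpoints section ties the BCVA and microperimetry changes to the study eye. The third functional parameter is different in kind: "a standardized assessment of the patient’s vision-related quality of life using a validated questionnaire, the NEI-VFQ-25". It is also named in the Secondary objectives.

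Analysis for the secondary endpoints makes three statements that bear on it:
- "Mean change from baseline in the NEI-VFQ-25 questionnaire to 6 to 8 weeks after treatment will be compared among the two treatment modalities".
- "the continuous secondary variables will be analyzed using an ANCOVA model with baseline as and treatment as factor". A word seems to be missing here; I read it as baseline entered as a covariate, as in the logistic model described just after.
- "The change from baseline in the NEI-VFQ-25 questionnaire results will be summarized descriptively".

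Fellow-eye data are collected: "BCVA will be assessed for both eyes at all evaluation visits", and the angiography schedule includes images of the non-study eye. No section uses them in an analysis.

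**The concern.** A questionnaire answered by the person reflects both eyes. If the second eye is diseased, its state and any treatment it receives feed into the score alongside the effect of the randomised treatment.

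Two consequences follow, and they differ in weight. Variation in fellow-eye disease and care adds person-level scatter that a model with only the baseline score and treatment leaves partly unexplained. That is noise. Separately, fellow-eye decisions can be made after the allocation is known. If they depend on the arm, the difference between arms mixes the study-eye effect with a fellow-eye effect. One conceivable route is that PDT-arm patients already receive verteporfin and HSML-arm patients do not. The document does not say that this happens.

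At stake is the reading of one secondary endpoint, in a protocol whose trial outline calls functional endpoints the most important ones from the patient's perspective.

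**Working it through.** **The plan's own figure.** There is no sample-size or power figure for the NEI-VFQ-25. The only one is for the primary endpoint, and I use its 78 per arm as an input. With the pooled-variance formula, two-sided α 0.05 and power 0.80, n = [1.960·√(2p̄(1−p̄)) + 0.842·√(p₁(1−p₁)+p₂(1−p₂))]² / (p₁−p₂)²:
- 80% v 50%: 39 per arm (stated 40).
- 72% v 50%, the pair being my assumption for the stated 22-point difference: 76 per arm, and 76 × 1.008 = 76.6, so 77, with an assumed two-look O'Brien-Fleming inflation (stated 78).

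Both are within two patients. No stated figure is in dispute.

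**Precision of the NEI-VFQ-25 contrast.** In SD units, SE = √(2/78) = 0.160. The difference detectable with 80% power is (1.960 + 0.842) × 0.160 = 0.449 SD.

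**Inputs the document does not give, hence assumed.** Share with an active fellow eye, b = 0.20 to 0.40. Between-arm difference in the fellow-eye treatment rate, d = 0 to 0.40. Effect of fellow-eye treatment on the score, e = 0.3 to 0.5 SD.

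**Case 1: fellow-eye treatment equal in both arms (d = 0).** Bias = b × 0 × e = 0, and type I error stays at 0.05. Take half of the active fellow eyes as treated and e = 0.5. The variance is then multiplied by 1 + (0.5b)(1 − 0.5b) × 0.25:
- b = 0.20: 1 + 0.10 × 0.90 × 0.25 = 1.0225. Power at a true difference of 0.45 SD falls from 0.802 to 0.794.
- b = 0.40: 1 + 0.20 × 0.80 × 0.25 = 1.04. Power falls to 0.787.

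**Case 2: fellow-eye treatment differs by arm.** Shift = b × d × e. Type I error = P(Z > 1.960 − shift/SE) + P(Z < −1.960 − shift/SE).

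| b | d | e (SD) | shift (SD) | type I error |
|---|---|---|---|---|
| 0.20 | 0.20 | 0.3 | 0.012 | 0.051 |
| 0.20 | 0.40 | 0.5 | 0.040 | 0.057 |
| 0.30 | 0.40 | 0.5 | 0.060 | 0.066 |
| 0.40 | 0.40 | 0.5 | 0.080 | 0.079 |

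The largest shift is 0.080/0.449 = 18% of the detectable difference. The sign depends on which arm has more effective fellow-eye treatment.

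**What each remedy can do.** Baseline fellow-eye acuity and activity are fixed before allocation and balanced by randomisation in expectation. Adjusting for them reduces scatter but cannot remove a difference that arises after allocation. Restricting to patients whose fellow eye is inactive at baseline largely closes that route, because the free-treatment rule applies to an active non-study eye. With b = 0.20 to 0.40, that subset has about 78 × 0.80 = 62 down to 78 × 0.60 = 47 per arm. Its detectable difference is 2.802 × √(2/62) = 0.50 SD to 2.802 × √(2/47) = 0.58 SD.

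**The case against.** The strongest reply is that bilateral disease precedes randomisation and is balanced in expectation. Comparing all patients under whatever fellow-eye care follows is then a legitimate question, and covariates for a secondary questionnaire usually belong in the analysis plan. Much of this stands. It is why the point is an improvement to a secondary analysis and not an error in the design. It does not dispose of the point, because the protocol itself fixes a model for continuous secondary variables, and that model leaves out relevant baseline data the trial already collects.

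Several stronger readings are tempting but unsupported:
- A reader might infer that the comparison is contaminated as a matter of fact. Bias needs a difference between arms in the rate, type or effect of fellow-eye treatment, and the document reports none.
- A reader might take the ANCOVA as the settled NEI-VFQ-25 analysis. The same section also promises only a descriptive summary, so the analysis is not settled.
- A reader might assume fellow-eye treatment occurs during follow-up. That is allowed, but no timing is stated. The analysis list takes the NEI-VFQ-25 only to 6 to 8 weeks, which leaves little time for it to act. The endpoint list adds 7 to 8 months, where there is more.
- A reader might extend the point to systemic adverse events. The protocol records relatedness, other suspect drugs or devices and concomitant medication, which should capture much of any fellow-eye verteporfin. Its statistical section specifies no between-arm test of systemic events.

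**Conclusion.** The concern holds in a limited form. The NEI-VFQ-25 comparison carries avoidable noise from the fellow eye, and it can be biased if fellow-eye treatment differs by arm. The two statements of its analysis conflict, and neither takes the fellow eye into account.

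Size and direction cannot be known from the document. Under the assumptions above, the effect ranges from a loss of about 1 to 2 points of power with no bias to a shift of at most 0.08 SD and a type I error near 0.08. These figures illustrate scale and are not estimates for this trial. The primary endpoint and the BCVA and microperimetry endpoints concern the study eye and are not affected by this point.

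**What to change.** In Analysis for the secondary endpoints, replace the conflicting statements on the NEI-VFQ-25 with one. Suggested wording:

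*Change in NEI-VFQ-25 score will be compared between arms by ANCOVA with treatment as factor and baseline score, baseline fellow-eye ETDRS BCVA and baseline fellow-eye active disease (yes/no) as covariates. A pre-specified sensitivity analysis will repeat the comparison in patients without active fellow-eye disease at baseline. Fellow-eye treatment will be reported by arm.*

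The covariates are for precision. The sensitivity analysis is the part that addresses arm-dependent fellow-eye treatment, and the report by arm shows whether it occurred. Fellow-eye treatment given after randomisation should not be entered as a covariate, because it may itself depend on the allocation.

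The freedom to treat the non-study eye is left unchanged. The cost is slightly more analysis work and, in the sensitivity analysis, a smaller sample that describes only patients with a quiet fellow eye at baseline. No extra visits or patients are needed.

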#### Inclusion criteria

The inclusion criteria are as follows:Male and female patients ≥18 years of age who are able to give written informed consent.Active cCSC.Subjective visual loss >6 weeks, interpreted as onset of active disease.SRF that includes the fovea on OCT scanning at baseline examination. *Note*: SRF does *no**t* have to include fovea on OCT to be eligible for treatment at control visit 1 as long as there is persistent SRF in the macula, which is interpreted as persistently active disease.Hyperfluorescent areas on ICG angiography.≥ 1 ill-defined hyperfluorescent leakage areas on fluorescein angiography with RPE window defect(s) that are compatible with cCSC.

#### Exclusion criteria

The participant may not enter the study if any of the following apply:Any previous treatments for active CSC in the study eye.Current treatment with corticosteroids (topical or systemic), corticosteroid use within 3 months before the possible start of trial treatment, or anticipated start of corticosteroid treatment within the first 7 to 8 months from the start of the trial period.Evidence of other diagnosis that can explain serous SRF or visual loss.BCVA <20/200 (Snellen equivalent).Profound chorioretinal atrophy in central macular area on ophthalmoscopy and OCT.Myopia >6D.Visual loss and/or serous detachment on OCT <6 weeks.Continuous and/or progressive visual loss >18 months or serous detachment on OCT >18 months.No hyperfluorescence on ICG angiography.Intraretinal edema on OCT.Contraindications (relative) for PDT treatment (pregnancy, porphyria, severely disturbed liver function). Pregnancy will not be routinely tested in female patients, but the possibility of pregnancy will be discussed during eligibility screening.Contraindications (relative) for fluorescein angiography or ICG angiography (known allergies especially against shellfish, previous reactions).Soft drusen in treated eye or fellow eye, signs of choroidal neovascularization on ophthalmoscopy and/or fluorescein angiography/ICG angiography.

### Study procedures

#### Screening and eligibility assessment

##### Identification of potential participants

Potential participants with cCSC will be identified in the participating trial sites, after being referred to the department by the general practitioner (GP) or referring ophthalmologists from other hospitals. Before screening, a visual acuity measurement, dilated ophthalmoscopy, fundus photography, OCT of the retina and choroid, autofluorescence imaging, and fluorescein and ICG angiography will already have been performed in most patients as part of standard clinical care. These examinations constitute most of the baseline examinations and therefore do not have to be repeated if screening and randomization is performed within 2 weeks after these examinations. Screening and baseline examinations/enrolment are performed on the same day if possible. The maximum duration allowed between screening and randomization is 2 weeks.

In addition to the examinations mentioned previously, the following information will be collected from patients who have been consented, at the baseline assessment; at control visit 1 and, if applicable, at control visit 2; and at the follow-up visit at 7 to 8 months after treatment visit 1:Demographic details - the date of birth, gender, race, smoking and drinking habits will be recorded on case report forms (CRFs).Medical history - details of any history of disease or surgical interventions will be recorded on CRFs.Concomitant medication - all over-the-counter or prescribed medication, vitamins, and/or herbal supplements will be recorded on CRFs.

